**Figure 2 F2:**
[figure not shown]
Flow chart of the PRISMA study.

### Procedure

#### Recruitment

Five out of seven Dutch University hospitals accepted the invitation to join the study. Participating hospitals are the Emma children’s hospital/Academic Medical Centre in Amsterdam, VU medical centre in Amsterdam, university medical centre Utrecht in Utrecht, St. Radboud university medical centre in Nijmegen and university medical centre Maastricht in Maastricht. A letter via their oncologist or psychologist informs patients and their caregivers about the study. Interested caregivers will be provided with a screening questionnaire concerning their child’s neurocognitive functioning (including items on attention functioning, memory and speed) and exclusion criteria (e.g. premorbid diagnosis of ADHD or ADD) to verify eligibility of the patient. If eligible for inclusion, the patient is invited for the pre training assessment. If applicable, a sibling will also be invited for assessment to participate in the control group. On the day of the pre training assessment, the informed consent form is signed by caregivers, the patient, and if applicable, the sibling.

#### Assessment

Assessments are conducted at one of the three cooperating EEG centers in the Netherlands; Pels institute in Amsterdam, Brainfact in Amsterdam, and EEG resource institute in Nijmegen. Patients are assessed on three occasions: pre training (T0), directly post training (T1), and six months post training (T2); see Figure 2. Assessments include neurocognitive testing, questionnaires filled out by patient, caregiver, and teacher, and a qEEG, see Table 1. Assessment of the siblings occurs only once, and is identical to the assessments used in patients with the exception of questionnaires filled out by parents and teachers.

**Table 1 T1:** Outcomes, measures and to whom it is administered

**Neurocognitive assessment**	**Measurement**	**T0**	**T1**	**T2**
Attention	Attention Network task (ANT) [28]	Patient/sibling (8–18)	Patient (8–18)	Patient (8–18)
Processing speed	Baseline Speed ANT [28]	Patient/sibling (8–18)	Patient (8–18)	Patient (8–18)
Memory	Visual Sequencing task	Patient/sibling (8–18)	Patient (8–18)	Patient (8–18)
	Digit Span (age appropriate Wechsler scale) [29,30]	Patient/sibling (8–18)	Patient (8–18)	Patient (8–18)
Intellectual functioning	Abbreviated WISC-III* [29]	Patient/sibling (8–16)	-	Patient (8–16)
	Abbreviated WAIS-III* [30]	Patient/sibling (17–18)	-	Patient (17–18)
Inhibition	Stop Signal task [31]	Patient/sibling (8–18)	Patient (8–18)	Patient (8–18)
Visuomotor integration	Tracking and Pursuit task	Patient/sibling (8–18)	Patient (8–18)	Patient (8–18)
**Questionnaires**				
Social/emotional functioning	SDQ child version [32]	Patient/sibling (8–18)	Patient (8–18)	Patient (8–18)
	SDQ parent version [32]	Caregiver (8–18)	Caregiver (8–18)	Caregiver (8–18)
	SDQ teacher version [32]	Teacher (8–18)	Teacher (8–18)	Teacher (8–18)
Self esteem	Dutch version SPPC [33]	Patient/sibling (8–11)	Patient (8–11)	Patient (8–11)
	Dutch version SPPA [34]	Patient/sibling (12–18)	Patient (12–18)	Patient (12–18)
Health related quality of life	Kidscreen 27 [35]	Patient/sibling (8–18)	Patient (8–18)	Patient (8–18)
Fatigue	CIS [36]	Patient/sibling (8–18)	Patient (8–18)	Patient (8–18)
Sleep disorder	SDSC [37]	Caregiver (8–18)	Caregiver (8–18)	Caregiver (8–18)
Attention	SWAN [38]	Caregiver (8–18)	Caregiver (8–18)	Caregiver (8–18)
Executive functioning	BRIEF parent version [39]	Caregiver (8–18)	Caregiver (8–18)	Caregiver (8–18)
	BRIEF teacher version [39]	Teacher (8–18)	Teacher (8–18)	Teacher (8–18)

Note: Intellectual functioning is assessed at T0 and T2 but not at T1. Siblings are assessed at T0 only.

*The following subtasks were administered: Arythmic, Similarities, Block Design, and Picture Completion.

SDQ = Strengths and Difficulties Questionnaires; SPPC/SPPA = Self Perception Profile for Children/Adolescents; CIS = Checklist Individual Strength; Sleep Disturbance Scale for Children; SWAN = Strengths and Weaknesses of ADHD-symptoms and Normal-behavior; BRIEF = Behavior Rating Inventory of Executive Functioning; WISC-III = Wechsler Intelligence Scale for Children – Third version; WAIS-III = Wechsler Adult Intelligence Scale – Third version.

##### qEEG

An EEG is recorded from the patients at three time points. A Quick-cap with NuAmp 10–20 electrodes international system from neuroscan is used, with 28 channels [40]; Fp1, Fp2, F7, F3, Fz, F4, F8, FC3, FCz, FC4, T3, C3, Cz, C4, T4, CP3, CPz, CP4, T5, P3, Pz, P4, T6, O1, Oz and O2. During the first three minutes an eyes-open resting EEG is registered, in the consecutive three minutes an eyes-closed resting EEG. After the resting EEG, event related potentials are measured during an odd ball and a go-nogo task. The Brain Resource International Database (BRID) [41,42], comprising EEG power spectra of over 4.000 healthy controls, provides normative data to quantify the EEG (qEEG) and obtain Z-scores for the participants in the current study.

##### Neurocognitive tests

To objectify the primary hypothesis of the study, that neurofeedback will improve neurocognitive functioning, different neurocognitive domains are assessed. The tests are conducted by one of the researchers or extensively trained research assistants and take approximately two and a half hours. Based on literature describing late effects in brain tumor patients, the following neurocognitive domains were targeted for assessment [43]: attention, processing speed, memory, intellectual functioning, inhibition, and visuomotor integration. Well-validated computerized and pencil-and-paper tests were selected to provide a comprehensive assessment of neurocognitive functioning before the training and the efficacy of neurofeedback (see Table 1).

##### Questionnaires

Our secondary hypothesis regards the impact of neuropsychological performance on psychosocial functioning [25,44]. Based on studies reports, the following domains are assessed using questionnaires: social/emotional functioning, self-esteem, and health related quality of life. Because of the reported decrease in fatigue after training in the pilot study, we also included questionnaires assessing fatigue and sleep disturbance [24]. In addition, two questionnaires on attention and executive functioning were added to assess caregiver and teacher rated neurocognitive functioning. Widely used, reliable, and validated questionnaires were selected in order to assess the domains of interest, as well as the effect of neurofeedback on these domains (see Table 1). Questionnaires were administered to either patient, caregivers or teacher, if applicable. The online questionnaires take approximately 30 minutes to fill out. In addition, as an interim measurement, caregivers fill in the attention questionnaire (SWAN [44]) one extra time, after the first 10 sessions of the patient.

### Power calculation

Power calculations used the neurocognitive measures as primary outcome measures. The calculations were done in the statistical program nQuery Advisor [45]. We expect that the neurofeedback will have a medium (d=0.5) to large effect (d=0.8) on neurocognitive functioning as measured at T1 and compared to T0, based on improvements found in children with ADHD who were trained with neurofeedback and on the improvements found in learning-impaired childhood cancer survivors treated with methylphenidate [12,15]. Given an effect size of 0.6 with alpha set at 0.05 (one-sided) and a power of 0.80, a minimum of 35 patients is required in both the neurofeedback group and the placebo group.

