### Statistical analyses

Intention-to-treat analyses will be conducted. Because of possible withdrawal before treatment starts, dropouts during the study, failure to fill out questionnaires, or research procedure violations, missing data will occur. Imputation of missing values will be carried out as much as possible to make intention-to-treat analyses feasible. Missing data will be imputed using Imputation and Variance Estimation Software [46].

Prior to the training (T0) we will assess differences between patients and siblings on neurocognitive and psychosocial functioning, using mixed modelling. Subsequently, we will conduct multivariate analysis of variance (MANOVA) to determine the effect of neurofeedback post-treatment (T1) on the primary and secondary outcomes, comparing the patients in the neurofeedback group to the patients in the placebo group. To control for possible differences in neurocognitive functioning prior to the training, T0 data will be included in the model as covariate. Finally, we will use repeated measures analysis for group (neurofeedback and placebo) x time (T0, T1, and six months follow-up, T2) to investigate the changes over time. To examine the possible effects of patient characteristics on the efficacy of the neurofeedback, the following variables will be assessed as covariates in the MANOVA and repeated measures analyses: age at assessment, age at diagnosis, diagnosis, time since diagnosis, and treatment modalities. All analyses will be conducted using SPSS. A *P*-value <0.05 will be considered significant.

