The design of PRISMA has some methodological pitfalls to take into account. Because of time factors and the population, this study might be at risk for losing patients during the treatment phase and during follow-up. With five year survival rates of approximately 65%, some patients may relapse [47], or they may discontinue their participation in the study. We increase comparability by employing three different training modules; however, the training might be less effective than an individualized training. The groups receiving each of the three treatment modules are small. Also, the group of brain tumor patients is heterogeneous, e.g. in terms of tumor diagnosis, tumor location, age at diagnosis, treatment, time since diagnosis, and time since end of treatment. It is well documented that these variables play an important role in neurocognitive outcomes. These heterogeneities may be reflected in our results.

In conclusion, if neurofeedback proves to be effective in improving neurocognitive deficits after treatment for a brain tumor, this would be a valuable addition to the currently available effective interventions for this vulnerable group of pediatric brain tumor survivors.

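### The 80% power is for a one-sided test of one outcome with no losses; it is not established for the planned non-directional MANOVA

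*Protocol article*

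**What the plan says.** The Power calculation section takes the neurocognitive measures together as primary and singles out none. It expects an effect between d=0.5 and d=0.8 at T1 compared with T0, then fixes the sample size: "Given an effect size of 0.6 with alpha set at 0.05 (one-sided) and a power of 0.80, a minimum of 35 patients is required". This number applies to each arm. The Abstract sets recruitment at 70 survivors, 35 to each arm, so the minimum is also the target.

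The Statistical analyses section names a different kind of test: "we will conduct multivariate analysis of variance (MANOVA) to determine the effect of neurofeedback post-treatment (T1) on the primary and secondary outcomes". T0 data enter as a covariate and P<0.05 is the threshold. That section mentions no one-sided test.

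On losses, the same section says that "missing data will occur" and plans imputation to support intention-to-treat analysis. The Discussion adds that "this study might be at risk for losing patients during the treatment phase and during follow-up". No loss rate is given.

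**The concern.** The sample size and the analysis are built on different tests, in three respects.

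- **Direction.** The calculation spends the whole 0.05 in one tail. A MANOVA F test rejects for departures in any direction, so a one-sided alpha has no counterpart in it.
- **Number of outcomes.** The calculation matches a single mean. The MANOVA tests several outcomes jointly, and its power depends on how many respond and how they correlate.
- **Losses.** The calculated minimum is the number recruited, although the article expects incomplete data.

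The 80% is the only sample-size justification given. If the trial finds no effect, that result will be read against 80% power, a figure the article has not shown to hold for the analysis that produced it.

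**Working it through.** **Inputs from the article.** d=0.6, alpha 0.05 one-sided, power 0.80, 35 per group (Power calculation); 70 recruited, 35+35 (Abstract); MANOVA at T1, T0 covariate, P<0.05 (Statistical analyses). Table 1 lists six neurocognitive tests at T1: Attention Network task, its baseline speed measure, Visual Sequencing, Digit Span, Stop Signal, and Tracking and Pursuit. Intellectual functioning is not assessed at T1.

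**Inputs assumed, because the article gives none.** Loss of 10-15%; inter-test correlation 0.3 or 0.5; T0-T1 correlation 0.5.

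**Step 1: reproduce the stated figure.** By the normal approximation, one-sided, n per group = 2(1.645+0.842)²/0.6² = 34.4, so 35. By the noncentral t distribution with 35 per group, the noncentrality is 0.6×√(35/2) = 2.510 on 68 df. The one-sided critical value is 1.668 and power is 0.7996. The article's arithmetic is right for that test.

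**Step 2: same outcome, two-sided.** The noncentrality is still 2.510, but the critical value becomes 1.995 and power is 0.697. Reaching 80% takes 45 per group (0.804; 44 gives 0.795). With 35 per group, 80% is reached at d of about 0.68 (0.801). At d=0.5, the lower end of the article's expected range, power is 0.54.

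**Step 3: allow for loss.** 35×0.90 = 31.5 and 35×0.85 = 29.75; take 31 and 30 per group, treating losses as complete-case exclusions.

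| Per group | One-sided 0.05 | Two-sided 0.05 |
|---|---|---|
| 35 | 0.800 | 0.697 |
| 31 | 0.755 | 0.642 |
| 30 | 0.743 | 0.628 |

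**Step 4: the MANOVA, without covariate or loss.** For p outcomes in two groups of n, power comes from the noncentral F distribution with p and 2n−p−1 df and noncentrality (n/2)D², where D² = δ′R⁻¹δ, δ holds the standardised effects and R the correlations. With p=6 and n=35 the df are 6 and 63.

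- All six at d=0.6, correlation 0.3: D² = 6×0.36/(1+5×0.3) = 0.864, noncentrality 17.5×0.864 = 15.12, power 0.80.
- All six at d=0.6, correlation 0.5: D² = 2.16/3.5 = 0.617, noncentrality 10.80, power 0.63.
- One of six at d=0.6, correlation 0.3: D² = 0.453, noncentrality 7.92, power 0.48.
- Three of six at d=0.6, correlation 0.3: D² = 0.987, noncentrality 17.28, power 0.86.

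**Step 5: the T0 covariate.** If d=0.6 is in raw T1 standard deviations, adjustment at T0-T1 correlation 0.5 makes the effective size 0.6/√(1−0.25) = 0.693. Two-sided single-outcome power is then 0.815 with 35 per group and 0.751 with 30. If d is already on the baseline-adjusted scale, there is no such gain and Step 2 stands.

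**The case against.** The strongest reply is that the planned analysis could reach 80% or more. Step 4 gives 0.80 and 0.86 for two plausible MANOVA patterns, and Step 5 gives 0.815 for a single outcome with the T0 covariate. The covariate belongs to the planned model, so figures without it are not the plan's own analysis. This stands. A reader might infer from the 70% benchmark that the trial has about 70% power at most. The article does not support that ceiling: MANOVA power turns on correlations and response patterns that it does not state.

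A second reply is that improvement is a directional hypothesis, so a one-sided alpha is legitimate. For a single outcome that is arguable, but the named test has no one-sided form. Even with the one-sided alpha granted, Step 3 leaves 0.755 to 0.743 for one unadjusted outcome once 10-15% are lost.

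A third reply is that imputation keeps every patient in the analysis, so 30 or 31 per group is not the planned sample. That is correct as to the analysis set. Imputation does not fully restore the information in unobserved outcomes, however, so the complete-case figures indicate the size of the loss rather than the planned analysis exactly.

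Finally, the scale of d is open. Describing the effect at T1 compared with T0 suggests a baseline-referenced effect, but change from T0 is not the same scale as a covariate-adjusted residual. The article settles neither.

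**Conclusion.** The concern holds as an inconsistency between the sample-size section and the analysis section; the sum itself is correct for the test it describes. Power of 80% is established only for a one-sided 0.05 comparison of one outcome at d=0.6 with no losses. It is not established for a non-directional MANOVA at P<0.05 with a T0 covariate and incomplete data.

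The size that can be stated firmly is the benchmark: about 70% for a two-sided test of one outcome at d=0.6 on the analysed scale, falling to about 63-64% under the assumed loss. For the MANOVA no single figure can be given. The illustrative cases run from 0.48 to 0.86 with six tests and 35 per group, before covariate gain or loss.

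**What to change.** Keep 70 patients and rewrite the power paragraph.

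1. Reconcile the one-sided alpha in Power calculation with the non-directional test in Statistical analyses.
2. Restate power at 35 per group for the test actually planned, two-sided or non-directional, including the T0 covariate and an allowance for loss.
3. Give the assumptions behind it: number of outcomes, how many are expected to respond, inter-outcome correlation, T0-T1 correlation and expected loss. Say whether d is in raw T1 standard deviations or baseline-adjusted residual ones.
4. If the 70% figure is quoted (80% at d of about 0.68), label it as the two-sided single-outcome benchmark. It should not stand in for the power of the MANOVA.

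The cost is a rewritten paragraph and a short calculation. The stated power will probably be less favourable. No extra patients are needed.

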### Statistical analyses

Intention-to-treat analyses will be conducted. Because of possible withdrawal before treatment starts, dropouts during the study, failure to fill out questionnaires, or research procedure violations, missing data will occur. Imputation of missing values will be carried out as much as possible to make intention-to-treat analyses feasible. Missing data will be imputed using Imputation and Variance Estimation Software [46].

Prior to the training (T0) we will assess differences between patients and siblings on neurocognitive and psychosocial functioning, using mixed modelling. Subsequently, we will conduct multivariate analysis of variance (MANOVA) to determine the effect of neurofeedback post-treatment (T1) on the primary and secondary outcomes, comparing the patients in the neurofeedback group to the patients in the placebo group. To control for possible differences in neurocognitive functioning prior to the training, T0 data will be included in the model as covariate. Finally, we will use repeated measures analysis for group (neurofeedback and placebo) x time (T0, T1, and six months follow-up, T2) to investigate the changes over time. To examine the possible effects of patient characteristics on the efficacy of the neurofeedback, the following variables will be assessed as covariates in the MANOVA and repeated measures analyses: age at assessment, age at diagnosis, diagnosis, time since diagnosis, and treatment modalities. All analyses will be conducted using SPSS. A *P*-value <0.05 will be considered significant.

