### Intervention

The neurofeedback training is performed at home or school using a Dell notebook (Inspiron N5030, 15.6 inch screen), with BioExplorer software, version 1.5 installed, and a portable Brainquiry PET neurofeedback device [26,27]. Reinforcement is provided by a self-selected movie that will be presented on the screen if the brain produces the desired activity, as detected by an electrode placed at Cz (see Figure 1). Each patient receives two sessions weekly for 15 weeks, 30 sessions in total. Each session takes 39 minutes to administer, divided in ten blocks of three-minutes training, alternated with one-minute breaks. In the breaks the patient will be instructed to sit quietly with the eyes closed.

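### Withdrawal before training and procedure violations are listed as causes of missing data to be imputed under an intention-to-treat label, while T1 and T2 are timed from the end of training, so some randomised children have no defined or comparable outcome visit

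*Protocol article*

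**What the plan says.** The Statistical analyses section of the protocol article commits to intention-to-treat and continues: "Because of possible withdrawal before treatment starts, dropouts during the study, failure to fill out questionnaires, or research procedure violations, missing data will occur". The next sentence reads: "Imputation of missing values will be carried out as much as possible to make intention-to-treat analyses feasible". An imputation package is named, but the imputation model is not described.

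The Assessment section lists the patients' test occasions as "pre training (T0), directly post training (T1), and six months post training (T2"). The Intervention section defines the course: "Each patient receives two sessions weekly for 15 weeks, 30 sessions in total". No outcome visit is timed from randomisation or from a planned calendar date.

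Three other places bear on the point:
- The Discussion acknowledges a risk of losing patients both while training is under way and afterwards, without giving a rate.
- The Background reports that all 9 children in the pilot study completed training.
- The Intervention section has research assistants record procedural deviations on a checklist after every session. The article does not link that record to the analysis.

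**The concern.** An intention-to-treat comparison uses the outcome of every randomised child, whatever training was received. Imputation is a fallback for outcomes that could not be obtained. Of the four events listed, only the unfilled questionnaire is by nature a missing outcome, and leaving the study usually leads to one. Withdrawal before treatment starts is a decision about training, and a procedure violation is a matter of conduct. A child can have either and still sit the tests.

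The visit schedule adds to this. With T1 and T2 tied to the end of training, a child who never starts has no end of training to count from. Followed as written, that child is imputed rather than observed.

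At stake is what the reported contrast means. If imputation draws mainly on children who completed the course in the same arm, it fills in the result expected after a full course. The estimate then drifts from the effect of being assigned neurofeedback towards the effect of completing it, still labelled intention-to-treat. If procedure violations are read broadly, events after randomisation could also influence which scores count.

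**Working it through.** **The plan's own figure.** The Power calculation section states "Given an effect size of 0.6 with alpha set at 0.05 (one-sided) and a power of 0.80" and concludes that "a minimum of 35 patients is required in both the neurofeedback group and the placebo group". With the normal approximation, n per arm = 2(z₀.₉₅ + z₀.₈₀)²/d² = 2(1.645 + 0.842)²/0.6² = 34.4, rounded up to 35; power at 35 is 0.81. The exact t-test gives 36, with power 0.7996 at 35. The figure reproduces and is not in dispute. It contains no allowance for loss or non-completion.

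**The timing, set side by side.** Thirty sessions at two a week take 15 weeks.
- Completer: T1 falls at about week 15 of training and T2 six months later.
- Child who stops after session 20, as an example: if tested directly after training ends, T1 falls at about week 20/2 = 10, five weeks earlier than for completers, and T2 moves with it.
- Child who never starts: neither visit has a date.

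**Illustration of size.** From the document: d = 0.6, applied here to completers. Assumed, because the document gives no value: the non-completion share p in the neurofeedback arm (10–20%, that is 3.5 to 7 of 35 children); the residual effect e in those children (0 to 0.3); no effect of non-completion on placebo outcomes; and imputation of all non-completers within arm from completers.

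As-assigned effect = 0.6(1 − p) + e·p. Overstatement = 0.6 divided by that value, minus 1.

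| p | e = 0 | e = 0.3 | Overstatement if imputation returns 0.60 |
|---|---|---|---|
| 10% | 0.54 | 0.57 | 5–11% |
| 15% | 0.51 | 0.555 | 8–18% |
| 20% | 0.48 | 0.54 | 11–25% |

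**Simulation of the mechanism.** Settings: 35 per arm; an assumed T0–T1 correlation of 0.6; non-completion at random in both arms; no benefit in non-completers; multiple imputation from arm and T0, fitted to completers; 10 imputations; 1,500 replicates.

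| Non-completion | Imputed | Full follow-up |
|---|---|---|
| 10% | 0.59 | 0.53 |
| 20% | 0.59 | 0.48 |
| 30% | 0.60 | 0.42 |

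**Dependence on the imputation model.** Suppose the model ignores arm and p is equal in both arms. Non-completers in each arm then receive the pooled completer mean, 0.6/2 = 0.3. The contrast becomes [0.6(1 − p) + 0.3p] − 0.3p = 0.6(1 − p), which is 0.54 at 10% and 0.48 at 20%. That equals the as-assigned effect if e = 0 and falls below it (0.57 and 0.54) if e = 0.3. At p = 0, as in the pilot, there is no bias under either model.

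**The case against.** The strongest reply is that the text describes why values may be absent and sets no rule for coding them. A reader might infer that every child short of 30 sessions is set to missing, or that scores already observed are discarded after a violation. The article says neither. The dropout it lists is from the study, which need not mean from training. A child who stops early can still be tested directly after the last session attended. A violation can also genuinely destroy a score, for example when a test is wrongly administered. All of this stands.

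A reader might also infer that the result will certainly be inflated. The document does not support that either. Inflation requires that non-completers go untested, that imputation is within arm under missing-at-random, and that they benefit less. None of the three is stated, the direction can change with the model, and the only completion figure in the article is 9 of 9, from a small pilot.

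Finally, a journal article condenses a fuller protocol, and the imputation model belongs in an analysis plan. Its absence is therefore no criticism here. This reply does not reach the visit schedule or the list of causes, which are stated. An analysis plan written later cannot recover outcomes that were never collected.

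**Conclusion.** The point holds in conditional form and should be acted on. It rests on two stated features: the list of events whose consequences are to be imputed under an intention-to-treat label, and outcome visits timed from the end of training. Together they leave a never-starter without a T1 or T2, and give an early stopper either a different interval from randomisation or no visit.

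The size is illustrative. Under the assumptions above, an as-assigned effect of 0.48 to 0.57 would be reported as about 0.60, an overstatement of roughly 5–25%. With no non-completion it is zero, and with another imputation model it could go the other way. Collecting and using the outcomes removes most of this dependence, so the remedy is worthwhile whichever direction the bias would take.

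**What to change.** 1. Time T1 and T2 for every randomised child from randomisation or planned start: at the planned end of the 15 weeks and six months after that, whatever number of sessions was received.
2. Invite children who stop or never start training to both visits, and record stopping training separately from withdrawing from assessment.
3. Limit procedure violations as a cause of missing data to tests that were not given or were invalidly administered. Analyse all other observed scores as observed.
4. Impute only outcomes that could not be obtained.

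The cost is a sentence in the assessment schedule, one in the analysis section, and visits for a few children that are already part of the schedule. Some families will still decline, so some imputation will remain. The estimated effect may be somewhat smaller. In the illustration with no residual benefit, one-sided power at 35 per arm falls from 0.81 to 0.73 at 10% non-completion and 0.64 at 20% (normal approximation), which is the price of estimating the effect of assignment.

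### The T1 MANOVA does not separate primary from secondary outcomes, and the stated 0.80 power was not derived for any MANOVA

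*Protocol article*

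**What the plan says.** The Background makes neurocognitive functioning the primary aim and psychosocial functioning, measured by questionnaire, the secondary one. The Power calculation section follows this: "Power calculations used the neurocognitive measures as primary outcome measures". It expects a "medium (d=0.5) to large effect (d=0.8) on neurocognitive functioning as measured at T1 and compared to T0". The sizing inputs are stated as "Given an effect size of 0.6 with alpha set at 0.05 (one-sided) and a power of 0.80". From these the section arrives at no fewer than 35 per arm.

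The Statistical analyses section then names one between-arm method for T1, a MANOVA comparing neurofeedback with placebo "to determine the effect of neurofeedback post-treatment (T1) on the primary and secondary outcomes". It adds that "T0 data will be included in the model as covariate". Significance is P<0.05, with no sidedness given. The section does not say whether the two outcome sets go into one model or several, or which test decides the primary question.

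Table 1 lists six neurocognitive measures at T1 (ANT, baseline speed, Visual Sequencing, Digit Span, Stop Signal, Tracking and Pursuit); intellectual functioning is not tested then. It also lists ten questionnaire measures at T1, counting the two age-specific self-esteem forms as one.

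**The concern.** There are two separate issues.

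**What the test answers.** The omnibus null of a MANOVA is that no outcome in the set differs between arms. If tests and questionnaires share one model, rejection shows only that something in the combined set differs. A parent or teacher questionnaire could produce it with no change on any neurocognitive test. The two readings of the sentence can give different conclusions on the primary aim, and the wording leaves that choice open.

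**What the power figure describes.** The sample size rests on one standardised difference and a one-sided alpha. A MANOVA omnibus test has no direction, spends one numerator degree of freedom per outcome, and has power that depends on the correlations between outcomes and on which outcomes respond. The 0.80 therefore cannot be carried over to it, whichever outcomes it contains.

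**Working it through.** **1. The plan's own figure.** Inputs from Power calculation: d=0.6, one-sided alpha 0.05, power 0.80.
- Normal approximation: n = 2(1.645+0.842)²/0.6² = 34.3, so 35 per arm, with power 0.807.
- Noncentral t at 35 per arm: noncentrality 0.6×√17.5 = 2.51, df 68, power 0.7996.
- Two-sided at 35 per arm: power 0.70 (t) to 0.71 (normal); 0.80 would need 44 to 45 per arm.

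The 35 thus reproduces as a one-sided comparison of two means on one outcome.

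**2. Formula for the planned test.** A two-group MANOVA with p outcomes and q covariates has an F statistic with p and 70−p−1−q df and noncentrality 17.5×δ′R⁻¹δ, where 17.5 = 35/2. With equal d on all p outcomes and common correlation ρ, δ′R⁻¹δ = p·d²/(1+(p−1)ρ).

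Assumptions not in the article: one score and one baseline per measure, the values of ρ, and the effects on questionnaires. The effect d is held at 0.6 after adjustment, so covariates cost degrees of freedom but earn no gain in precision.

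**3. Neurocognitive outcomes only** (p=6, q=6, df 6 and 57), d=0.6 on all six. For example, at ρ=0.3: 6×0.36/2.5 = 0.864, and the noncentrality is 15.12.

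| ρ | Noncentrality | Power |
|---|---|---|
| 0.1 | 25.2 | 0.97 |
| 0.3 | 15.1 | 0.80 |
| 0.5 | 10.8 | 0.63 |

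**4. All outcomes in one model** (p=16, q=16, df 16 and 37). The columns give the probability of a significant omnibus test at within-set correlation 0.3 and 0.5. Cross-set correlation is the correlation between tests and questionnaires.

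| True effect | Cross-set correlation | 0.3 | 0.5 |
|---|---|---|---|
| d=0.6 on all 16 | same as within | 0.60 | 0.39 |
| d=0.6 on the 6 tests only | same as within | 0.93 | 0.99 |
| d=0.6 on the 6 tests only | zero | 0.50 | 0.35 |
| d=0.6 on the 10 questionnaires only | same as within | 0.96 | 0.99 |
| d=0.6 on the 10 questionnaires only | zero | 0.56 | 0.37 |

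The last two rows show that a joint test rejects far more often than 5% when no neurocognitive test has changed. The first three show that the power of a joint test can fall on either side of 0.80.

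**5. Effect of crediting the baselines.** If the T0–T1 correlation were 0.7 (assumed), d would scale by 1/√(1−0.49). Power at ρ=0.3 and 0.5 would then be 0.99 and 0.93 for the six-outcome model, and 0.93 and 0.73 for the 16-outcome model.

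**The case against.** The strongest reply is that the sentence names a method and the outcomes it covers, and fits one MANOVA per outcome set equally well. The context helps that reading. The article ties the tests to the primary hypothesis and the questionnaires to the secondary one, and it gives the reason for the T0 covariate as baseline differences in neurocognitive functioning. The singular model proves little, since other analyses covering many outcomes are also named in the singular. No omnibus p-value is named as the decision rule, and a condensed article may leave the make-up of each model to the full protocol or analysis plan.

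Much of this stands. A reader might infer that the plan fits all outcomes together; the text permits that but does not state it. A reader might also infer that the analysis lacks 0.80 power. The article gives no number of scores, correlations or secondary effects, and several plausible settings above exceed 0.90. Nor can it be said that the secondary outcomes cause the mismatch: the neurocognitive-only MANOVA also differs from the one-sided, single-outcome basis (0.63 at correlation 0.5), and when only the tests respond and all correlations are equal, the joint model is the more powerful one.

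The reply does not reach two things. The article does state the T1 test, and its wording does not tie the primary conclusion to the neurocognitive measures. The gap between the sizing and a multivariate test is present under both readings.

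**Conclusion.** The point holds in a limited form. The consequence of the unseparated outcome sets is conditional: only if they are modelled jointly does a significant omnibus test fail to isolate the primary question. In the settings examined, an effect of 0.6 on the questionnaires alone makes that test significant with probability from 0.37 to 0.99, depending mainly on how strongly the questionnaires correlate with the tests.

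The power point is unconditional. The stated 0.80 describes a different test from the one planned. The true figure cannot be fixed from the article and may be higher or lower. All multivariate figures rest on assumed outcome counts, correlations and effect patterns. Those that give no credit for baseline adjustment will be too low if T0 scores predict T1 scores well.

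**What to change.** - State that the primary efficacy test is fitted to the T1 neurocognitive scores only, with their own T0 scores as covariates.
- Analyse the questionnaires in separate models labelled secondary.
- Restate the power of that primary test at the planned 35 per arm, giving its sidedness, the number of scores and the assumed correlations, including any assumed T0–T1 correlation.

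This takes a few sentences and one power calculation, with no new data or assessments. The costs are running more than one model and a restated power that may be less favourable than 0.80.
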